### Data analysis

2.9

The analyses will be performed on the intention-to-treat (ITT) basis, including all randomized patients. We will also perform a per-protocol analysis excluding women who did not use the DiaCompanion I app for at least 50% of expected meals to explore the efficacy of the system under optimal use.

Quantitative data will be assessed for normality using the Kolmogorov-Smirnov test. Log transformation could be used where appropriate. The data will be presented as mean and SD for normally distributed parameters and as median with quartiles for non-normally distributed characteristics. The distribution of binary or ordinary characteristics will be described as N (%).

The significance of differences in scale parameters (such as the percentage of postprandial capillary glucose values above target, the number of in-patient visits, etc.) between the control and intervention groups will be assessed by the Student’s t-test for normally distributed ones and Mann-Whitney test for ordinal and non-normally distributed characteristics. To compare the distribution of binary or ordinary characteristics (ex., rate of patients requiring insulin therapy during pregnancy, LGA, SGA, etc.) the χ2 criterion or Fisher’s exact test will be used. The Spearman correlation coefficient will be used to assess the relationship between two variables. We will use ANOVA repeated or nonparametric analogue for the analysis of repeated measurements (gestational weight change). The critical level of significance of the null statistical hypothesis will be assumed to be 0.05.

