### DiaCompanion I intervention

2.6

Participants in the intervention group are required to enter all food intakes into the app. They are also required to enter blood glucose measurements before main food intakes (breakfast, dinner and lunch) to enable the prediction of postprandial BG level. In case of a high predicted BG they are encouraged to change the amount and/or content of the planned meal in a manner that will lead to a predicted BG within target range.

Women in the intervention group are recommended to send their electronic diaries (standardized reports) to their endocrinologists every week in order to get feedback. The doctors check the food records and glucose levels and send back recommendations on dietary corrections if necessary. In case of revealing indications for insulin therapy, the women are appointed to an office visit within a few days.

The participants of the intervention group have only two scheduled visits to endocrinologists during pregnancy (at baseline and on the 35-37^th^ gestational week (GW)) if they are included after the 20^th^ GW. Those included before the 20^th^ GW are also invited at the 24^th^ GW. Additional visits are appointed in case of the appearance of indications to insulin treatment (repeated fasting capillary glucose of ≥5.1mmol/L or a 1-hour postprandial value of ≥7.0 mmol/L during 1-2 weeks). Two or more abnormal values during 1-2 weeks of monitoring are required to commence insulin treatment according to Russian national guidelines (16).

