### Standard care

2.7

Women in the control group will have a standard of care without a mobile app. According to Russian national guidelines, women diagnosed with GDM receive guidance on diet, physical activity and self-monitoring of BG with capillary glucose meters. They are required to self-record their fasting, pre-prandial and 1-hour postprandial BG values and they are also advised to self-record their food intakes in a paper diary at home. They are attending the maternity clinic every 2-3 weeks where an endocrinologist reviews their readings and diary. In case of repeated fasting capillary glucose of ≥5.1mmol/L or a 1-hour postprandial value of ≥7.0 mmol/L during 1-2 weeks or one reading above 9.0 mmol/L at any time of day, participants are instructed to call the clinic and schedule an additional visit to reconsider indications for insulin treatment.

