## Discussion

3

Our mobile-based recommendation system DiaCompanion I differentiates from existing GDM apps by the ability to predict postprandial BG level at the time of food intake planning and by providing real-time personalized recommendations on the ways of hyperglycemia prevention.

There are published and ongoing trials of the effect of personalized diets by prediction of glycaemic responses on glycaemic control in prediabetes and type 2 diabetes mellitus. However, these analogues are not intended for pregnant women (18, 19).

The authors of a recent review investigating the awareness and use of the smartphone applications (app) with respect to management of GDM concluded that mobile apps provided personalized health care services, patient care improvement, and enhanced patient’s compliance toward blood glucose monitoring and treatment (20). A relatively large RCT by Mackillop et al. (21) reported less preterm births and fewer cesarean deliveries despite the fact that there was no significant change in BG levels between the control and the intervention groups.

In another scoping review, the authors investigated mHealth apps intended for use with GDM and concluded that there were limited mHealth apps for GDM that incorporated AI or AI-based decision support (22).

It is well known that learning how to manage the results of self- tracking and adhering to a diet requires efforts from women with GDM, as associations between lifestyle, nutrition and PPGR are complex and difficult to identify, especially during the first weeks after GDM diagnosis (23). As DiaCompanion I provides recommendations at each time when a high BG is predicted, we expect the most significant difference in glucose control parameters within the first weeks after GDM diagnosis.

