Our system does not consist of an app only, as participants in the intervention group are supposed to generate diary reports from the app weekly and send it to their physicians. Using this approach, we substitute most of in-person communications with a feedback based on diary analysis by means of return messages. We believe that the combination of automated feedback from the app before each meal intake with weekly feedback from a healthcare professional will further increase the efficacy of the intervention while reducing the number of in-patients visits. Apart from reducing the burden on health care facilities, we expect a reduction in total time spent for patients communicating by endocrinologists or other health care providers dealing with BG and diet control in patients with GDM.

However, this approach also poses challenges. It is difficult to differentiate the influence from automated recommendations based on PPGR prediction and the influence of weekly medical feedback. Another limitation of our study is the lack of BG prediction and insulin doses adjustment for patients treated with insulin. Women requiring insulin will be recorded and followed until delivery but they will not be able to use the prediction function. It is supposed to work incorrectly in such patients because we have not included insulin treated women in the population used for the development of PPGR prediction models. It is a task for our future research to develop such models.

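### The per-protocol rule can exclude women from the app arm only, on behaviour after randomisation, so that comparison is not randomised and can be biased, probably but not certainly towards the app

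*Protocol article*

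**What the plan says.** Section 2.9 (Data analysis) sets the main analysis set: "The analyses will be performed on the intention-to-treat (ITT) basis, including all randomized patients". It then adds: "We will also perform a per-protocol analysis excluding women who did not use the DiaCompanion I app for at least 50% of expected meals", and gives the purpose as "to explore the efficacy of the system under optimal use". The between-group tests named in that section are unadjusted (t-test or Mann-Whitney for scale outcomes, chi-squared or Fisher for binary ones).

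Section 2.7 (Standard care) says of controls: "Women in the control group will have a standard of care without a mobile app". On diet recording, "they are also advised to self-record their food intakes in a paper diary at home". No adherence criterion is set for them.

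Section 2.6 (DiaCompanion I intervention) sets what full use means: "Participants in the intervention group are required to enter all food intakes into the app". The Discussion adds: "Women requiring insulin will be recorded and followed until delivery but they will not be able to use the prediction function".

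**The concern.** An exclusion rule defined by app use cannot be met or failed by a woman who was never given the app. Every control stays in, including those who record poorly or follow the diet poorly. Their counterparts in the intervention arm are taken out. Randomisation balanced the two full arms. It does not balance the full control arm against the part of the app arm that kept logging.

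There are reasons to expect the remaining app users to have the better prognosis. The protocol's Discussion accepts that self-tracking and "adhering to a diet requires efforts from women with GDM", so a woman who logs at least half her meals may well be one who also keeps to the diet. A second possible route is insulin. Women who start it lose the prediction function, and if that reduced their counted app use, membership of the per-protocol set would depend partly on glycaemia after randomisation.

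At stake is how the result is read. The stated purpose describes a causal quantity that this comparison does not estimate. In an open-label trial of an app built by the authors, a significant per-protocol difference beside a null intention-to-treat result would be easy to over-interpret.

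**Working it through.** The plan gives no figure for this analysis: neither the share expected to fall below 50% use nor any link between use and glycaemia. Both are assumptions here, shown as ranges.

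**Inputs from the protocol.** Planned means 15% and 11%, SD 10 (Sample size, 2.10). The difference is 15 − 11 = 4 points and 4/10 = 0.4, which agrees with the stated standardised effect. Total 216 randomised 1:1 (2.1), so 108 per arm. The planned 25% dropout leaves 108 × 0.75 = 81 per arm.

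**Assumptions.** No app effect. App use is a latent normal variable with correlation ρ to a better outcome. The lowest share q of users is removed from the app arm only.

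**Bias.** Apparent benefit = SD × ρ × φ(z_q)/(1 − q), where z_q is the q-quantile of the standard normal distribution.
- q = 0.20: φ = 0.280, so 10 × ρ × 0.280/0.80 = 3.50ρ, giving 0.70 (ρ = 0.2) and 1.40 (ρ = 0.4).
- q = 0.40: φ = 0.386, so 10 × ρ × 0.386/0.60 = 6.44ρ, giving 1.29 (ρ = 0.2) and 2.58 (ρ = 0.4).

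The range of 0.70 to 2.58 points is 18% to 64% of the planned 4.

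**False-positive rate.** With n controls and n(1 − q) app users, SE = 10 × √(1/n + 1/(n(1 − q))). The two-sided rate at nominal 5% follows from bias/SE. In the worst cell:
- n = 108: SE = 10 × √(1/108 + 1/64.8) = 1.57; 2.58/1.57 = 1.64; P(Z > 1.96 − 1.64) ≈ 37%.
- n = 81: SE = 10 × √(1/81 + 1/48.6) = 1.81; 2.58/1.81 = 1.42; P(Z > 1.96 − 1.42) ≈ 29%.

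| Excluded | ρ | Bias (points) | Rate, 108 per arm | Rate, 81 per arm |
|---|---|---|---|---|
| 20% | 0.2 | 0.70 | 8% | 7% |
| 20% | 0.4 | 1.40 | 16% | 13% |
| 40% | 0.2 | 1.29 | 13% | 11% |
| 40% | 0.4 | 2.58 | 37% | 29% |

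Simulation with normal data and the pooled t-test agrees with the table. With a skewed percentage outcome (beta distribution, mean 15, SD 10) and an unequal-variance t-test, the worst cell rises to about 43% at 108 per arm and about 33% at 81. The 43% and 29% therefore differ partly by model, not only by dropout.

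**Checks on cause and direction.** With ρ = 0 the bias is zero and the error rate stays at about 5%. With ρ = −0.3 and 30% excluded, the bias is 10 × 0.3 × 0.348/0.70 = 1.5 points against the app.

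**The case against.** Intention-to-treat on all randomised women is the main analysis. The per-protocol analysis is an addition, and its own wording says it is exploratory. That stands, and it limits the harm: nothing in the document rests an efficacy conclusion on this comparison.

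A reader might infer that the analysis favours the app even if the app does nothing. The documents do not support that as a fact. No passage links app use to glycaemia, and well-controlled women might stop logging while women with high readings log more. What the text does establish is the one-arm selection, and with it the possibility of bias.

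A reader might also infer that the rule removes insulin-treated women, and so the women with the highest glucose. The text does not say so. It takes away the prediction function only. The app also tracks food and insulin doses, and all food intakes are to be entered, so these women can still count as users. Indications for insulin include fasting values, whereas the primary outcome is postprandial. How use is counted after insulin start is detail that a condensed article may leave to the analysis plan, so its absence is not a fault here.

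A larger illustration is tempting: if the excluded 20% had a mean of 25%, those remaining would average (15 − 0.2 × 25)/0.8 = 12.5, a bias of 2.5 points. Under the model above that needs 3.50ρ = 2.5, so ρ ≈ 0.71, well outside the assumed 0.2-0.4. It should not be used as support.

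Finally, an instrumental-variable estimate is not a clean replacement. Assignment also brings weekly remote feedback and fewer scheduled visits, which reach low users too. A common rule for both arms, such as half of expected glucose readings, would still select on behaviour after randomisation. Both objections stand and shape the fix.

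**Conclusion.** The point holds as a should-fix matter. The text itself establishes that the per-protocol rule can act in one arm only, that it uses post-randomisation behaviour, and that no adjustment or matching criterion is stated. Loss of the randomised comparison does not depend on the direction of any bias.

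Bias towards the app is likely if women who log more have better glycaemia, but this is expected rather than proven. The sizes in the working are illustrations that rest on an assumed exclusion share and correlation. They show that the selection alone could produce more than half the planned effect in the worst case considered, and a small distortion in the mildest. The higher false-positive rates assume full retention and are lower after the planned dropout.

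**What to change.** 1. State that conclusions on efficacy rest on the intention-to-treat analysis alone.
2. Keep the 50%-use comparison if wanted, but label it non-randomised and supportive, and drop the description of it as efficacy under optimal use.
3. Add, as a sensitivity analysis, a complier-average estimate that keeps all randomised women, with randomised arm as instrument and at least 50% app use as exposure. Because controls have no app, this is the intention-to-treat difference divided by the share p of the app arm reaching 50% use, so it is zero whenever the intention-to-treat difference is zero. State beside it that the exclusion restriction is strained, because weekly remote feedback and the reduced visit schedule also reach low users.
4. Define counted app use so that losing the prediction function at insulin start is not scored as non-use.

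The cost is analysis-plan wording and a few lines of code. The interval is wider than the naive one. For example, with p = 0.7 and 108 per arm, the standard error is roughly 10 × √(2/108)/0.7 = 1.94 points, against 10 × √(1/108 + 1/75.6) = 1.50 for the one-sided exclusion. The estimate also carries an assumption that must be declared.

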### Study design and setting

2.1

This study is an interventional open-labeled randomized controlled trial. A total of 216 women with GDM will take part in this trial performed in the Almazov National Medical Research Centre. Patients are randomized 1:1 to the intervention or control group. The intervention group receives DiaCompanion I app and standard antenatal care with the reduced number of visits to endocrinologists. The control group receives standard antenatal care. Patients participate in the study from recruitment (between 12 and 32 completed weeks of pregnancy) until delivery and will be invited to the follow-up visit at 3-6 months postpartum. The study protocol follows the Standard Protocol Items: Recommendations for Interventional Trials (SPIRIT) (11). Study design and data collection are shown in **Figure 1**. Please find the detailed information on the intervention and data collection in the sections below.

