### Proposed outcome measurement

2.8

Primary Outcome is the percentage of postprandial capillary glucose values above target (>7.0 mmol/L) in the time frame from randomization up to delivery. The women will be asked to perform 6 measures a day. Capillary glucose values will be retrieved from the glucose meter, and if not available, from the woman’s diary.

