Secondary outcome measures are:1. Rate of patients requiring insulin therapy during pregnancy⚬ Rate of patients requiring insulin therapy (either basal or prandial)⚬ Rate of patients requiring prandial insulin therapy2. Capillary glucose values in the following time frames: within 2 weeks after randomization , at gestational weeks 35-37, and in the period from randomization up to delivery.⚬ Capillary fasting glucose values, mmol/L⚬ Capillary preprandial glucose values, mmol/L⚬ Capillary postprandial glucose values, mmol/L3. The proportion of women with glucose values within target in the following time frames: within 2 weeks after randomization, at gestational weeks 35-37, and in the period from randomization up to delivery.⚬ The proportion of women with fasting glucose values within the target⚬ The proportion of women with postprandial glucose values within the target4. Mean incremental area under the blood glucose curve 2 hours after meals (iAUC120) according to 7-day continuous glucose monitoring 1-2 weeks after randomization and at the 35-37^th^ GW.5. Hypoglycaemia⚬ Severe hypoglycaemia: requiring the assistance of another person to actively correct the level of glycaemia and neurological symptoms⚬ Documented symptomatic hypoglycaemia: event during which typical symptoms of hypoglycaemia are accompanied by a measured capillary glucose concentration <3.9 mmol/L⚬ Asymptomatic hypoglycaemia: event not accompanied by typical symptoms of hypoglycaemia but with a measured capillary glucose concentration <3.3 mmol/L6. Maternal metabolic parameters at 35-37^th^ GW (the level of HbA1c, Fasting insulin, Fasting glucose, HOMA-IR index, serum triglyceride levels).7. Gestational weight change by the time of delivery⚬ Gestational weight change during pregnancy, kg⚬ Gestational weight change between inclusion and delivery, kg8. Large (>90th percentile) for gestational age infant9. Small for gestational age (< 10th percentile) infant10. Birth weight, kg11. Birth weight ≥ 4000 g; ≥ 4500 g (yes/no)12. Neonatal hypoglycaemia defined as glucose levels <2,2 mmol/L in the first 4 hours of life or <2,5 mmol/L at 4–24 hours of age (yes/no) (17).13. Shoulder dystocia (yes/no)14. Birth injury, any of the following: plexus injury, clavicle, humeral, or skull fracture (yes/no)15. Preterm delivery (yes/no)16. Apgar score at 1 and 5 minutes from birth17. Low Apgar score: 5-min Apgar score < 7 (yes/no)18. Jaundice requiring phototherapy (yes/no)19. Neonatal respiratory distress syndrome (yes/no)20. Admission to neonatal intensive care unit during the three days following birth (yes/no)21. Umbilical cord blood C-peptide, ng/mL22. Cesarean delivery rate23. Induction of labor rate24. Need for operative vaginal delivery rate (forceps or vacuum-assisted vaginal delivery)25. Preeclampsia (blood pressure ≥ 140/90 mmHg on two measurements four hours apart and proteinuria of at least 300 mg/24 hours or 3+ or more on dipstick testing or proteinuria/creatinuria >30 in a random urine sample)26. Pregnancy-induced hypertension in women with no known hypertension before pregnancy (blood pressure ≥ 140/90 mmHg on two measurements four hours apart without proteinuria, and required anti-hypertensive therapy)27. The number of in-patient visits to endocrinologists in the time frame from randomization to delivery.28. Results of oral glucose tolerance test 3 months postpartum.29. Acceptance/satisfaction of 2 strategies at 35-36^th^ GW (Evaluation of the patient satisfaction with their treatment for GDM with a scale: give a score of 0 to 100: 0 not satisfied; 100 totally satisfied).30. Patient satisfaction evaluated through a questionnaire at 35-36^th^ GW.

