
We will use a 10-question questionnaire with multiple-choice questions, questions with numeric answers on a scale from 0 (fully unsatisfied) to 10 (fully satisfied), and open-ended questions.

The timetable of the planned visits and measurements is shown in **Table 2**.

**Table 2 T2:** Measurements timeline.

Measurements for both groups	Baseline	24^th^ GW*	35-36^th^ GW	Birth		Postpartum (3- 6 months)
Questionnaires (SF36, STAI, treatment attitude)	**x**		**x**			
Patient satisfaction questionnaire			**x**			
Physical examination (height, weight, blood pressure, oedema)	**x**	**x**	**x**			**X**
Medtronic CGM sensors	**x**		**x**			
Laboratory blood tests	**x**		**x**			
Cord blood samples and HUVECs				**x**		
Infant’s anthropometry, Apgar score, BG 1 hour after birth				**x**		
OGTT						**x**
Fecal, urine and saliva samples	**x**		**x**			
BG readings (glucometer)	**x**	**x**	**x**			
Measurements only for the intervention group:						
Data from DiaCompanion I app (BG readings, food tracker)	**x**	**x**	**x**			
Technology acceptance questionnaire			**x**			

*Visit at the 24^th^ GW will be scheduled for the participants included before the 20^th^ GW.

GW, gestational week; SF36, Short Form-36, STAI, State-Trait Anxiety Inventory, CGM, continuous glucose monitoring; BG, blood glucose; HUVECs, human umbilical vein endothelial cells; OGTT, oral glucose tolerance test.

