### Sample size

2.10

The sample size for the RCT was calculated as the number of participants needed to test the statistical significance of the difference between the two means (reduction in mean percent of BG readings exceeding target glycaemic levels from 15 to 11%, SD 10%) at a significance level of 0.05 and with a power of 0.80 for d/SD values = 0.4, including 25% dropout.

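### The primary comparison is fixed as an unadjusted two-sample test: valid, but it gives up precision that values known at or before baseline could supply

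*Protocol article*

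**What the plan says.** Proposed outcome measurement (2.8) defines the endpoint: "Primary Outcome is the percentage of postprandial capillary glucose values above target (>7.0 mmol/L) in the time frame from randomization up to delivery". It gives one percentage per woman.

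Data analysis (2.9) covers it explicitly, "The significance of differences in scale parameters (such as the percentage of postprandial capillary glucose values above target, the number of in-patient visits, etc", and says that such differences will be "assessed by the Student’s t-test for normally distributed ones and Mann-Whitney test for ordinal and non-normally distributed characteristics". No covariate-adjusted model is described for this or any other outcome. The only other model mentioned is a repeated-measures ANOVA, with gestational weight change as its example.

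Entry is wide: "Patients participate in the study from recruitment (between 12 and 32 completed weeks of pregnancy) until delivery". Table 1 gives the limits as at least 12 and under 32 weeks. Under Participants (2.2), diagnosis may rest on fasting glucose from early pregnancy, on a later glucose tolerance test, or on both.

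Table 2 schedules height, weight, glucometer readings and "Laboratory blood tests" at baseline, without listing what the laboratory tests contain. It also ticks continuous glucose monitoring (CGM) at baseline, whereas secondary outcome 4 is measured "according to 7-day continuous glucose monitoring 1-2 weeks after randomization".

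Sample size (2.10) is built on this target, in percentage points: "reduction in mean percent of BG readings exceeding target glycaemic levels from 15 to 11%, SD 10". Alpha is 0.05, planned power is 80% and the standardised effect is 0.4; a 25% dropout is said to be allowed for. The stated total is 216.

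**The concern.** The percentage of postprandial readings above target probably depends on where a woman starts: how far into pregnancy she is, her body size and her glycaemia at diagnosis. A woman entering at 12 weeks contributes up to about 20 more weeks of readings than one entering just before 32 weeks. The Discussion expects the largest difference in the first weeks after diagnosis, so length of follow-up also bears on the outcome. In an unadjusted test all of this variation stays in the error term.

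The plan's own background points the same way. The models behind the app use anthropometry, laboratory data and individual patient characteristics, along with meal data, to predict postprandial glucose. The sponsor therefore already treats such variables as informative.

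At stake is the width of the confidence interval and the chance of detecting the planned 4-point difference. This matters more because 216 women less 25% dropout give less than the planned power under a two-sided test.

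**Working it through.** **Inputs from the document.** Means 15% and 11%, so a difference of 4 points; SD 10 points; standardised effect 4/10 = 0.4; alpha 0.05; power 0.80; dropout 25%; total 216, allocated 1:1.

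**Assumed.** Two-sided testing (sidedness is not stated). R², the share of outcome variance explained by the covariates (no figure is given), taken as 0.04, 0.10, 0.20 and 0.30.

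**Step 1: the plan's own figure.** A two-sided t-test at effect 0.4 with 80% power needs 99.1 women per arm, rounded up to 100, or 200 evaluable. Allowing for 25% dropout, 100/0.75 = 133.3, rounded up to 134 per arm, or 268. The stated 216 is not reproduced. One-sided, 78 per arm gives 78/0.75 = 104 per arm, or 208, which is not 216 either.

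**Step 2: evaluable women.** 216/2 = 108 per arm. 108 × 0.75 = 81 per arm after the planned dropout.

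**Step 3: effect of adjustment.** A prognostic covariate reduces the residual SD to 10 × √(1 − R²), so the effective standardised difference is 0.4/√(1 − R²). The standard error of the difference with n per arm is 10 × √(1 − R²) × √(2/n). Power is from the two-sided t-test.

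| Assumed R² | Effective d | SE at 81 per arm (points) | Power at 81 per arm |
|---|---|---|---|
| 0 (as planned) | 0.400 | 1.57 | 71.6% |
| 0.04 | 0.408 | 1.54 | 73.3% |
| 0.10 | 0.422 | 1.49 | 76.0% |
| 0.20 | 0.447 | 1.41 | 80.8% |
| 0.30 | 0.478 | 1.32 | 85.6% |

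Reaching 80% at 81 per arm needs R² of about 0.17 (normal approximation) to 0.18 (t-test).

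**Step 4: no dropout.** With all 108 per arm, unadjusted power is 83.3%; at R² = 0.20 it is 90.5%.

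**Step 5: which covariates the document supports.**
- Gestational age at entry: known for every woman, because it defines eligibility.
- BMI: not named, but it follows from the baseline height and weight in Table 2. Pre-pregnancy weight is not listed.
- Diagnostic fasting glucose: obtained before randomisation, but the criteria are joined by and/or, so completeness has to be confirmed.
- HbA1c: named with a time point only at 35-37 weeks. It is usable only if the baseline laboratory tests include it.
- CGM and glucometer readings ticked at baseline: CGM falls after randomisation according to outcome 4. Glucometer timing relative to randomisation is not given, and app data, which cannot precede allocation, carry the same baseline tick.

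**The case against.** The strongest reply is that nothing here is an error. An unadjusted comparison of randomised groups is unbiased, and its type I error already allows for chance imbalance. That stands: this is a point about efficiency. A reader might infer that the primary result would be biased or invalid; the documents do not support that.

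It can also be said that a condensed article leaves the adjusted model to an analysis plan not shown. This carries less weight, because the article does not leave the test open. It names the primary outcome and assigns it an unadjusted test, so a plan that adjusted would depart from it.

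The gain is assumed. The sponsor's prediction models concern single meals and use meal data, so they give no R² for a woman-level percentage. At R² = 0.04 the gain is under 2 points. A reader might conclude that adjustment restores 80% power; nothing in the document establishes the R² this needs.

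The 72% figure also depends on two-sided testing and the full 25% loss. One-sided, 81 per arm gives about 81%. It reflects the mismatch between 216 and its inputs, which adjustment may offset but does not correct.

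Two further readings go too far. HbA1c, pre-pregnancy BMI and a diagnostic fasting value are not shown to be available for every woman. Nor does the article's silence on stratification prove that allocation was unstratified, and the point does not rely on that.

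Finally, a linear model of percentages still gives a woman with few readings the same weight as one with many, and it replaces a possible rank comparison with a mean difference. Both are true. The second agrees with the sample-size section, which is framed in means.

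**Conclusion.** The point holds as a recommendation to improve efficiency. The stated primary analysis ignores prognostic information that the trial will have at or before baseline, in a population whose entry spans about 20 weeks of pregnancy. The planned test remains valid.

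The size of the gain is not known from the document. Over the assumed range of R² from 0.04 to 0.30, power at 81 per arm rises by about 2 to 14 points from 71.6% (two-sided, with women who drop out contributing no outcome). The benefit does not depend on the shortfall: with no dropout, R² = 0.20 would still add about 7 points, from 83.3% to 90.5%.

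**What to change.** Before outcome data are examined, and by a documented amendment, make the primary analysis a linear model of the woman-level percentage on:
- arm;
- gestational age at randomisation, as a continuous term;
- BMI from baseline height and weight;
- one glycaemic measure taken before randomisation and confirmed to be recorded for all women: diagnostic fasting glucose, or baseline HbA1c if it is among the baseline laboratory tests.

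Use robust standard errors, report the adjusted mean difference with its 95% confidence interval, and keep the unadjusted comparison as a sensitivity analysis. Do not use CGM or glucometer readings taken after randomisation as covariates. State in the amendment that the target is a difference in means.

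No new measurement should be needed if the glycaemic covariate is confirmed as already recorded. The costs are the amendment, matching protocol and registry wording, and a check of covariate completeness. Because the trial is open-label and has been recruiting since January 2022, the amendment should record its date and reason and confirm that comparative outcome data had not been examined. The sample-size calculation needs its own correction.
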